#### ***11.5.1.4 Analysis of Immunogenicity***

Immunogenicity endpoints will be analysed at Day 28 and Day 56 compared to baseline (Day 0), and Day 56 compared to Day 28 to define the primary response to the vaccine, at Day 208 compared to Day 56 to describe the antibody levels in response to the booster dose and further at Day 180 compared to Day 56 to describe the antibody persistence of the primary vaccination, and Day 365 compared to Day 208 to describe the antibody persistence. GMTs and GMCs will be presented along with 95% Confidence Intervals.

A vaccine responder will be defined as a subject with sera reactivity by ELISA against both antigens (PfMSP-119 and PfF2) greater than background reactivity (average plus three standard deviations) of pre-vaccinated sera (17).

*Information contained in this publication is the property of EVI and ICGEB and is confidential and will not be disclosed to third parties without written authorization from EVI and ICGEB. No part of this document may be reproduced, stored in a retrieval system or transmitted in any form or by any means -electronic, mechanical, recording or otherwise - without the prior authorization of EVI and ICGEB*

[figure not shown][figure not shown]

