13. **Urine Drug Screen:** Urinalysis to test for drugs of abuse (benzodiazepines, opioids, amphetamine, cocaine, and THC) will be undertaken once at the Screening Visit (Visit 2) and subsequently on D28, D180 and D365. If the subject tests positive during screening period, he will be excluded from the study. If the subject tests positive on D28, D180 or D365, he will be immediately discontinued from the study.
14. **Randomisation Number:** Subjects, who fulfill all the eligibility criteria, will be randomised into the study with the assignment of a unique randomisation number.
15. **Diary Cards:** A pre-printed diary card will be given to the subject with detailed completion instructions on the day of vaccine administration and will be collected on Day 28 after each dose of vaccine. This diary card will be used for the record of solicited AEs (Day 0 through Day 14) and unsolicited AEs (Day 0 through Day 28). Thus three (3) such diary cards will be given to each subject. The Investigator will collect, review and transcribe the data from diary cards to CRF at pre-defined time-points.
16. **Record Immediate Reactogenicity:** Following vaccination on Days 0, 28 and 180, all subjects will be monitored at the site every 30 minutes till 3 hours for any immediate reactions with special emphasis on allergic/anaphylactic reactions. Vital signs will be done after the subject has been resting quietly for at least 5 minutes. BP will be taken in the supine position.
17. **Record Solicited AEs:** Each subject will record solicited AEs from vaccination through Day 14 after each dose on the diary card. These solicited AEs will be reviewed and transcribed from diary cards to CRF by the Investigator on Days 7, 14, 35, 42, 187 and 194. In addition, solicited AEs will be independently assessed by the investigator Days 14, 42 and 194 and the data directly entered in the CRF.
18. **Serology (ELISA and IFA):** Blood samples will be collected for serology assessment (ELISA and IFA) on Days 0, 28, 56, 180, 208 and 365. On Days 0, 28 and 180, blood samples will be collected prior to vaccination.
19. **Serology (IgG subclasses and GIA):** Blood samples will be collected for serology assessment (IgG subclasses by ELISA) on Days 0, 28, 56, 180, 208 and 365 and for GIA on Days 0, 56, 208 and 365 only. On Days 0, 28 and 180, blood samples will be collected prior to vaccination.

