### 4.6.2 Secondary Endpoint(s)

- The humoral response to the candidate vaccine antigen will be assessed (quantitative assessment) by measuring the level of IgG antibodies developed against PfMSP-119 and Pff2 by ELISA on Days 0, 28, 56, 180, 208 and 365
- The humoral response to the candidate vaccine antigen will be assessed (qualitative assessment) to verify the ability of the IgG antibodies developed against PfMSP-119 and Pff2 to recognise the native proteins, namely, PfMSP1 and EBA175 in late stage *P. falciparum* schizonts and merozoites by IFA on Days 0, 28, 56, 180, 208 and 365.

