## **6.2 Packaging, Labelling and Storage of Study Vaccines**

DLS/designated facility will receive the investigational vaccine from BBIL under controlled conditions and the record of the temperature during transit as well during transient storage will be maintained by DLS/designated facility, as applicable. Similarly, the control vaccine will be received from Serum Institute of India and the temperature records both for in-transit status and during transient storage will be maintained by DLS/designated facility.

Study vaccines (both investigational and control vaccines) will be packed in individual boxes per subject called as “vaccine packs”. A total of 45 such boxes will be prepared, and numbered from 1 to 45, according to the randomisation list. In addition, two (2) packs will be prepared (one each for the study and control vaccine) and utilised for site training. These two (2) trial packs will be separately labelled as “FOR TRAINING PURPOSE ONLY, NOT FOR CLINICAL TRIAL USE” and labelled accordingly. Extra supply of study vaccines of 20% will be included as contingency in case of any breakage during preparation.

There will be two kind of vaccine packs: 1) The primary vaccination pack will contain two (2) doses of the assigned vaccine (study/control) requested for the first two vaccination at D0 and D28, 2) The booster pack will contain one (1) dose of the assigned vaccine (study/control) requested for the booster vaccination at D180, along with the required quantity of adjuvant and WFI, as applicable. The syringes and needles of the required specifications for reconstitution and vaccine administration for assigned vaccine will be available at the site and used by the site team as required.

*Information contained in this publication is the property of EVI and ICGEB and is confidential and will not be disclosed to third parties without written authorization from EVI and ICGEB. No part of this document may be reproduced, stored in a retrieval system or transmitted in any form or by any means -electronic, mechanical, recording or otherwise - without the prior authorization of EVI and ICGEB*

[figure not shown][figure not shown]

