## 11.5 Analysis Methods

### 11.5.1 Statistical Model, Hypothesis Testing and Tests

No statistical hypothesis can be set up for the safety and immunogenicity data as sample size is limited. The analysis shall be descriptive as the sample size does not allow any comparison between groups. Categorical Variables will be summarised by vaccine groups as frequency, percentages and 95% confidence interval. Continuous Variables other than titers and Concentrations will be summarised by vaccine groups as Mean, SEM, Median, Minimum, Maximum, inter-quartile range/range. The proportion of subjects that received three doses without experiencing grade 3 adverse events will be estimated by Exact Binomial proportion (Proportion and 95% confidence interval).

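### The only booster contrast named is Day 208 against Day 56; adding the paired Day 208/Day 180 ratio would show the rise after dose 3 directly, at no extra sampling cost

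*Supplement*

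**What the plan says.** Section 11.5.1.4 of the protocol lists six immunogenicity contrasts: Day 28 and Day 56 against Day 0, Day 56 against Day 28, Day 208 against Day 56, Day 180 against Day 56, and Day 365 against Day 208. The one given to the third dose is "at Day 208 compared to Day 56 to describe the antibody levels in response to the booster dose". Day 180 appears once, as "Day 180 compared to Day 56 to describe the antibody persistence of the primary vaccination". On summary measures the section says "GMTs and GMCs will be presented along with 95% Confidence Intervals".

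The third dose is given on Day 180; section 6.2 describes the pack as "requested for the booster vaccination at D180". Section 4.6.2 schedules IgG measurement "by ELISA on Days 0, 28, 56, 180, 208 and 365", and section 4.6.3 gives the same days for the IgG subclasses. Footnotes 18 and 19 to Table 1 state that "On Days 0, 28 and 180, blood samples will be collected prior to vaccination". The Day 180 serum is therefore a true pre-booster sample. The growth inhibition assay (GIA) is the exception, with samples on Days 0, 56, 208 and 365 only.

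Section 11.5.1 sets the status of the analysis: "The analysis shall be descriptive as the sample size does not allow any comparison between groups". Section 11 calls itself an outline and refers full details to a separate SAP, which is not shown.

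**The concern.** A dose-specific response is most directly read against the sample taken just before that dose. The plan does this for dose 1 (Day 28 against Day 0) and dose 2 (Day 56 against Day 28). For dose 3 the reference is the level reached 28 days after dose 2, although 124 days lie between that sample and the booster. Any waning in that interval enters the contrast and counts against the booster.

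What is at stake is interpretation. A clear rise after dose 3 could appear as a Day 208/Day 56 ratio near or below 1. If dosages wane at different rates, differences between them on this contrast would partly reflect waning. The trial is the first in humans, and section 11.2 plans an interim analysis on data to 28 days after dose 3, so this contrast would be reported early.

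**Working it through.** The documents contain no titre, fold-rise or sample size calculation for this comparison, so there is no figure of the plan's own to reproduce. The plan does not say how its comparisons are expressed. Because it reports geometric means, I take them as ratios, that is, differences on the log scale.

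**Inputs from the protocol**
- Dose 2 on Day 28, dose 3 on Day 180.
- Sampling on Days 56, 180 (pre-dose) and 208.
- Interval from dose 2 to its follow-up sample: 56 − 28 = 28 days. From dose 3: 208 − 180 = 28 days.
- Interval over which waning can occur: 180 − 56 = 124 days.

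**Identity.** Within a subject, log(D208/D56) = log(D208/D180) + log(D180/D56). Averaged over the same subjects and exponentiated:

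D208/D56 = (D208/D180) × (D180/D56).

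The named contrast therefore falls short of the rise over the pre-booster level by the factor D56/D180. A numerical check on simulated titres for 10 subjects confirmed that this is exact when the same subjects are used throughout.

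**Size, under an assumption.** With exponential decay, D56/D180 = 2^(124/half-life). The half-lives are my assumption. The last column takes a 4-fold rise from Day 180 to Day 208, also assumed.

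| Assumed half-life (days) | Fall, Day 56 to Day 180 | D208/D56 if D208/D180 = 4 |
|---|---|---|
| 30 | 17.55 | 4/17.55 = 0.23 |
| 45 | 6.75 | 4/6.75 = 0.59 |
| 60 | 4.19 | 4/4.19 = 0.95 |
| 90 | 2.60 | 4/2.60 = 1.54 |
| 180 | 1.61 | 4/1.61 = 2.48 |

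The same 4-fold rise would read as a fall, no change or a moderate rise, depending only on waning. With no waning the two ratios coincide.

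**What the planned contrasts already give.** Write X = log(D208/D56) and Y = log(D180/D56), both planned. Then log(D208/D180) = X − Y, so the point estimate follows exactly for subjects with all three samples. Its variance is Var(X) + Var(Y) − 2Cov(X, Y). The covariance is not among the planned summaries, so the paired interval cannot be recovered from the two reported contrasts. With 10 subjects per dosage, that interval matters as much as the estimate.

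**Where it applies.** Total IgG by ELISA and the IgG subclasses have a Day 180 sample, so Day 208/Day 180 can be computed. GIA has none, so Day 208/Day 56 is the only contrast there between the post-dose-3 and post-dose-2 samples.

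**The case against.** The strongest defence is that the section speaks of antibody levels in response to the booster, not of a fold-rise caused by it. Days 56 and 208 are each 28 days after a dose, so comparing them is like for like and answers a sensible question: does dose 3 take antibody above what two doses reached? This stands, and the contrast should be kept.

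The waning term is also planned in the same sentence. A reader who sees Day 208/Day 56 near 1 beside Day 180/Day 56 of about 0.24 (the 60-day case, 1/4.19) can see that antibody rose after dose 3. This largely stands too. What remains missing is the direct paired estimate with its interval.

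Section 11 is only an outline, and the SAP may add the ratio. That is why the point is offered as a better choice of contrast rather than as an omission. Still, the protocol does choose a booster contrast, and it departs from the pre-dose reference used for doses 1 and 2.

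A reader might infer that a working booster will be reported as having failed, or that choices of schedule and dosage will be misled. The documents do not support this. Only one schedule is tested, every dosage gets the same contrasts, no decision rule is attached to Day 208/Day 56, and a reading of no response would require ignoring the planned Day 180/Day 56 result.

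Finally, Day 208/Day 180 is not a perfectly pure measure of dose 3, since antibody from the primary doses may keep waning over those 28 days. It is nonetheless the closest available.

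**Conclusion.** The point holds as an improvement. Day 208 against Day 56 is a legitimate comparison of post-dose levels, but as the only contrast named for the booster it does not show the rise produced by dose 3. It understates that rise by whatever fall occurs between Days 56 and 180. That fall is about 1.6- to 17.5-fold for assumed half-lives of 180 to 30 days under simple exponential decay; the documents give nothing with which to narrow the range.

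It would be tempting to say that the booster response is understated as a matter of fact. That goes too far: it requires waning, which the documents do not quantify, and it requires the target to be the rise over the pre-dose level, which the section does not state. No data are lost. The endpoint is secondary and descriptive, so no error rate, power or safety conclusion is affected. This is not a must-fix error.

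**What to change.** In section 11.5.1.4 and the SAP:

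1. Add the within-subject Day 208/Day 180 geometric mean ratio with a 95% confidence interval, per antigen and dosage, as the measure of the rise after dose 3. Apply it to total IgG by ELISA and to the IgG subclasses, and report the number of subjects with both samples.
2. Keep Day 208/Day 56, relabelled as the post-dose-3 level relative to the post-dose-2 level. Retain it for GIA, which has no Day 180 sample.
3. Leave Day 180/Day 56 as the persistence measure and present it beside the other two.

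Specify this before the interim analysis of Day 208 data. The analysts are unblinded, and a contrast added later could look data-driven. The cost is a few lines of text and one extra table column; the visits, blood draws and assays are already planned.

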### 5.3 Number of Subjects

- A sufficient number of subjects will be screened to enrol a total number of 45 subjects in the study.
- 30 subjects will receive the investigational vaccine (i.e. JAIVAC-1—Montanide ISA 720) with 10 subjects in each cohort and
- 15 subjects will receive the control vaccine (i.e. Hepatitis B vaccine) with 5 subjects in each cohort.

Subjects who are discontinued from the study prior to the first vaccination will be replaced. However, subjects who are discontinued from the study after the first vaccination will be considered as drop-outs and will not be subsequently replaced.

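### Section 11.5.1.4 plans six within-subject visit comparisons of antibody levels but names only GMTs and GMCs with 95% CIs, so the change itself gets no stated estimate or interval

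*Supplement*

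**What the plan says.** Section 11.5.1.4 sets out the comparisons by purpose:

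- Primary response: "Immunogenicity endpoints will be analysed at Day 28 and Day 56 compared to baseline (Day 0), and Day 56 compared to Day 28".
- Booster response: "at Day 208 compared to Day 56 to describe the antibody levels in response to the booster dose".
- Persistence of the primary vaccination: "at Day 180 compared to Day 56 to describe the antibody persistence of the primary vaccination".
- Later persistence: "Day 365 compared to Day 208 to describe the antibody persistence".

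That makes six contrasts: D28/D0, D56/D0, D56/D28, D208/D56, D180/D56 and D365/D208. Every subject is bled for ELISA on all six days (Table 1, footnote 18), so each contrast compares subjects with themselves.

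For antibody levels the section then says "GMTs and GMCs will be presented along with 95% Confidence Intervals". It also defines a responder: "A vaccine responder will be defined as a subject with sera reactivity by ELISA against both antigens". Section 11.5.1 would summarise that as a percentage with a 95% CI.

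The general rule for continuous data does not reach antibody levels, because section 11.5.1 reads "Continuous Variables other than titers and Concentrations will be summarised by vaccine groups as Mean, SEM, Median". On attrition, section 5.3 says that "subjects who are discontinued from the study after the first vaccination will be considered as drop-outs and will not be subsequently replaced".

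**The concern.** The quantities of interest are changes: how far antibody rises after two doses, how the level after the third dose compares with Day 56, and how much is lost by Days 180 and 365. No ratio, fold rise, log difference or interval for a change is named. The protocol does specify change elsewhere: section 11.5.1.3 has vital-sign changes from pre-vaccination calculated and tabulated. Antibody level, a secondary endpoint, has no equivalent.

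With complete data a reader can divide two GMTs to obtain the point estimate of the ratio. The reader cannot obtain its interval from the two visit-wise intervals, because the within-subject correlation is not shown. Once someone drops out, the two GMTs rest on different subjects, and even the point estimate may move for reasons unrelated to antibody. With 10 subjects per dosage, both effects are large enough to blur statements on booster response and persistence.

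**Working it through.** **Inputs from the documents.** Ten subjects per investigational dosage (section 11.1.1); six contrasts on repeated samples (section 11.5.1.4); 95% confidence level. No SD, correlation, expected fold change or sample-size calculation is given, so there is no planned figure to reproduce.

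**Assumptions, not in the documents.** Log10 SD s = 0.5, equal at both visits; within-subject correlation rho from 0.3 to 0.8; normality on the log scale.

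**Formulas.** Each result is the factor by which the estimate is multiplied and divided to reach its 95% limits.

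- GMT at one visit: 10^(t[n−1] × s / √n)
- Ratio of two visits, pairing not used: 10^(t[2n−2] × s × √(2/n))
- Ratio of two visits, paired: 10^(t[n−1] × s × √(2(1−rho)/n))

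**Numbers for n = 10**, with t[9] = 2.262 and t[18] = 2.101:

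- One visit: 2.262 × 0.5 / 3.162 = 0.358; factor 2.28
- Unpaired ratio: 2.101 × 0.5 × 0.447 = 0.470; factor 2.95
- Paired ratio, rho 0.3: 2.262 × 0.5 × 0.374 = 0.423; factor 2.65
- Paired ratio, rho 0.5: 2.262 × 0.5 × 0.316 = 0.358; factor 2.28
- Paired ratio, rho 0.8: 2.262 × 0.5 × 0.200 = 0.226; factor 1.68

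The one-visit factor equals the paired factor at rho 0.5 only because 2(1 − 0.5) = 1.

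**Dependence on the SD.** The ratio of paired to unpaired width on the log scale does not depend on s. It is 0.90 at rho 0.3, 0.76 at rho 0.5 and 0.48 at rho 0.8. With n = 10, pairing narrows the interval once rho exceeds 1 − (2.101/2.262)² ≈ 0.14.

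**Direction of the loss.** In a simulation of 100,000 trials with n = 10, the unpaired 95% interval covered the true ratio 99.1% of the time at rho 0.5 and 99.9% at rho 0.8; the paired interval covered about 95%. Not using pairing therefore costs precision and does not make the interval too narrow.

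**Day 0 contrasts.** Subjects must test negative for anti-malarial antibodies at pre-screening (Table 1, footnote 3). If Day 0 values sit at the assay floor with SD near 0 (an assumption), the SD of the log difference is about 0.5 and the ratio factor for D28/D0 or D56/D0 is about 2.28, the same as for the post-dose GMT alone. Little is lost there. The loss falls on D56/D28, D208/D56, D180/D56 and D365/D208.

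**Drop-out effect.** Suppose one of 10 subjects lies 1.0 log10 from the group mean and is missing at the later visit. The mean of the other nine differs from the mean of all ten by 1.0/9 = 0.111 log10, a factor of 10^0.111 = 1.29, with no change in anyone's antibody.

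**The case against.** The strongest objection is that section 11 calls itself an outline and leaves full details to a separate SAP, and section 11.4 leaves the description of variables to it. That SAP is not shown and may well specify paired ratios. This stands to the extent that nobody can say the final analysis will lack them. It does not remove the point: 11.5.1.4 already goes as far as naming the contrasts and the summary statistic, and the statistic does not match the contrasts. Section 10.5 finalises the SAP after the database listings have been reviewed, the analysts are unblinded (section 11.1.3), and the interim analysis in section 11.2 runs to 28 days after the third dose, when five of the six contrasts are available. Section 11.2 says the interim details will be in the SAP, but the documents do not say that it is final by then. Naming the statistic in the protocol closes that gap cheaply.

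A second objection is that the trial is descriptive, with no hypothesis and no power calculation. This stands against any argument from error rates or power. It does not excuse leaving undescribed the quantity that the plan sets out to compare.

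A reader might also infer that pairing will be ignored, that no valid interval will exist, or that GMTs are the only immunogenicity result planned. The documents do not support these readings. The text is silent on pairing. A GMT interval is valid for the GMT, and an unpaired interval for a ratio would be conservative. A responder proportion with a CI is also foreseen, although as a threshold against pre-vaccination background it does not measure a booster rise or a decline.

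**Conclusion.** The point holds as a gap in specification that should be closed. Section 11.5.1.4 promises within-subject comparisons and names, for antibody levels, a statistic that does not quantify them or their uncertainty. Under the stated assumptions the interval for a visit-to-visit ratio narrows from a factor of 2.95 to 2.28 or 1.68 when pairing is used. The absolute factors depend on the assumed SD; the relative gain depends only on rho and the number of subjects. The four contrasts between post-dose visits carry the weight. The two Day 0 contrasts lose little if baseline is near the assay floor. The primary safety objectives are not affected.

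**What to change.** Add to section 11.5.1.4, after the sentence on GMTs and GMCs, and carry into the SAP:

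> For each antigen, vaccine group and listed pair of visits, the geometric mean of the within-subject ratio (later visit / earlier visit) will be presented with a 95% CI, obtained by back-transforming the paired t interval of the individual log10 differences, using subjects with both samples. These ratios are the descriptive basis for statements on primary response, booster response and persistence, and will be shown alongside the visit-wise GMTs/GMCs and the responder proportions. The number of subjects in each ratio will be given.

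The cost is a short paragraph and one further table per antigen, with no new samples, visits or subjects. The downside is that a subject missing one of the two samples leaves that ratio, while staying in the visit-wise tables. For scale, with two of 10 subjects lost (n = 8, same SD) the paired factor is 2.62 at rho 0.5 and 1.84 at rho 0.8, still below the unpaired 2.95 from all 10. At rho 0.3 it would be 3.12, slightly wider.
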